### 2.2. Participant Selection for Cohort Study

The patient sample will be recruited at the recruitment centre from workers directly affiliated with the Trial Centre or indirectly connected to it as part of the food supply chain. Patient screening will be carried out by a multidisciplinary team and will aim to determine the subject’s eligibility according to the following inclusion and exclusion criteria.

Inclusion criteria: (i) workers affiliated with the Trial Centre or indirectly connected to the Trial Centre as part of the food supply chain; (ii) adults aged between 18 and 65 years; (iii) willingness to undergo specific tests: assessments of nutritional status, investigations into quality of life and emotional–affective wellbeing; (iv) signed informed consent.

Exclusion criteria: (i) pregnant women will be excluded to avoid physiological changes related to pregnancy affecting the measurements; (ii) workers following specific diets for medical or religious reasons, which may not be representative of the general food supply chain population, will be excluded; (iii) unsigned informed consent.

In addition to excluding pregnant women and individuals following medically prescribed diets, information on chronic medical conditions and medications known to influence serotonin metabolism, oxidative stress, inflammatory status, or body composition will be systematically collected. Rather than excluding these participants, such variables will be treated as potential confounders and incorporated into the analytical strategy (e.g., sensitivity analyses, adjusted models) to maintain ecological validity while minimizing biomarker bias.

Once eligibility has been assessed, participants will be provided with an informed consent form, which they will be required to read and sign before being formally enrolled in the study. The entire process will be overseen by the principal investigator, who will ensure that participants are properly informed and that their voluntary participation is respected, in accordance with the procedures described below.

### 2.3. Data Management

As both Promoter and Trial Centre, the Don Gnocchi Foundation retains exclusive ownership of the data collected during the study, in accordance with Regulation (EU) No. 536/2014 [27] and Ministerial Decree of 30 November 2021 [28].

Upon obtaining informed consent, data will be initially collected on paper Case Report Forms (CRFs) and subsequently entered in pseudonymized form into a secure electronic database by the investigator.

Specifically, each participant will be assigned a unique alphanumeric identification code (Subject ID). The correspondence between the participant’s personal data and the Subject ID will be recorded in a dedicated “Subject Identification Log”, accessible only to the principal investigator and authorized collaborators. This document will be destroyed upon completion of the study. Data collection will be carried out by the Trial Centre, and data will be entered into the electronic database in a pseudonymized format. The principal investigator will oversee quality assurance procedures. Pseudonymization will be performed in such a way that individuals accessing the database cannot, under any circumstances, trace the identity of the study participants. Only the principal investigator and authorized collaborators will have access to the information required to re-identify participants enrolled at the Trial Centre.

### 2.4. Data Confidentiality Statement

The data of participants involved in the research project will be processed in full compliance with the right to privacy, in accordance with Regulation (EU) No. 2016/679 (General Data Protection Regulation–GDPR) [29].

Information relating to clinical, demographic, and genealogical data will be collected, processed, stored, and used for the purposes of diagnosis, preventive investigation, and care, ensuring appropriate confidentiality and compliance with privacy legislation (Regulation (EU) No. 2016/679–GDPR [29] and the General Authorisation for the Processing of Genetic Data No. 8/2016 issued by the Italian Data Protection Authority on 15 December 2016) [30].

### 2.5. Ethical Consideration

The study will be conducted in accordance with Italian legislation and in compliance with the principles of the Declaration of Helsinki. Relevant ethical code references include (1) Helsinki: Articles 4, 5, 7; (2) Helsinki: Article 6; (3) Helsinki: Articles 9, 10, 11.

All activities will be carried out in accordance with the provisions of European Regulation 2017/745 [31] and the subsequent Italian Legislative Decree of 5 August 2022, No. 137, as updated on 12 April 2023 [32].

The principal investigator confirms adherence to the procedures described in this protocol and to the principles of Good Clinical Practice (GCP). The study sponsor ensures the protection of all clinical and non-clinical personal data collected during the project, in compliance with national data-protection regulations (D. Lgs. 196/2003) [33].

It is the responsibility of the investigators, or personnel delegated by them, to obtain informed consent after providing participants with clear and complete information on the study aims, procedures, anticipated benefits, and potential risks. Participants must also be explicitly reassured that refusal to participate or withdrawal at any time will not result in any disadvantage. The informed consent form includes all details necessary for participants to give free and reasoned consent. Before signing, each participant will be invited to read the form carefully. The accompanying information sheet outlines the assessments to be performed, any risks associated with them, and the pseudonymization procedures applied to protect personal identity. Pseudonymization allows re-identification only in two situations: (i) when findings relevant to a participant’s health emerge and the individual has authorized recontact for this purpose; and (ii) when the participant requests the deletion of their personal data from the study database.

The study protocol underwent ethical review by the local ethics committee, Comitato Etico Territoriale Lazio Area 1, and received approval on 20 February 2025.

## 3. Procedure

The evaluation of worker well-being will integrate validated measures of quality of life and emotional–affective functioning with nutritional and physical indicators, together with selected biological markers, as shown in Figure 2.

### 3.1. Anamnestic and Lifestyle Information

Once enrolled, the following data will be recorded for each participant: demographic and general health information and smoking habits; use of medications, supplements and nutraceuticals; and type of work and number of working hours per day, week and year and active breaks during work.

### 3.2. Nutritional Status

#### 3.2.1. Anthropometric Measurement Assessment

Anthropometric measurements will include assessments of height and body weight. Weight will be assessed to an accuracy of 0.1 kg on a calibrated scale. Measurements will be taken in the morning after an overnight fast, without heavy clothing or shoes. Height will be recorded and reported in metres (m). Body mass index (BMI) at T0 and T1 will be calculated, expressed in kg/m^2^, and circumferences (arm, calf, waist and hips) will be measured and reported in centimetres (cm). The waist-to-hip ratio (WHR) will also be calculated.

#### 3.2.2. Body Composition Assessment

Body composition assessment will be assessed using a tetrapolar bioelectrical impedance analysis (BIA) at a single frequency of 50 kHz (101 anniversary sports edition, Akern s.r.l., Florence, Italy). Bioelectrical impedance analysis (BIA) was performed using four certified electrodes (BIATRODES, Akern, Florence, Italy), arranged in two pairs positioned 5 cm apart on the metacarpal and metatarsal regions of the non-hemiparetic side. Measurements were taken with participants lying supine and with limbs positioned symmetrically. Prior to electrode placement, the skin was cleaned to ensure optimal conductivity and reduce potential artefacts. Individuals with fever or hypothermia were not assessed, as body temperature can influence electrical resistance. Hydration status was clinically evaluated before conducting BIA, and participants showing marked dehydration or peripheral edema were excluded. Subjects with implanted pacemakers were also not eligible. All operators received specific instructions to ensure correct data acquisition and minimize potential measurement errors.

Raw bioelectrical data consisted of Resistance (R, Ω) and Reactance (Xc, Ω) acquired under standardized conditions. These raw measures were exported and processed using the Bodygram^®^ analysis software (v. 3.3.19, Akern, Florence, Italy), which automatically computes derived impedance parameters according to the manufacturer’s validated algorithms (tissue hydration percentage, nutritional index, resistance, reactance, phase angle, standardized phase angle (SPhA), total body water, extracellular water, intracellular water, lean mass, fat mass, body cell mass, musculoskeletal mass, appendicular muscle mass, basal metabolic rate, and total daily energy expenditure).

Bioelectrical Impedance Vector Analysis (BIVA) will also be derived from raw data. Specifically, R and Xc were standardized by height (H, m) to obtain R/H and Xc/H, and the resulting values were plotted on the R–Xc plane to generate individual impedance vectors. The software provides BIVA graphical output as well as derived indices (e.g., vector length and phase angle), enabling subsequent group-level comparison of vector position. For an extensive description of BIVA, see Guerrini et al. [34].

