### 1.2. Aim and Hypothesis

This exploratory observational study primarily aims to assess whether differences in nutritional status and body composition—as indexed by bioimpedance-based assessment of body cell mass and hydration—exist between sedentary and physically active workers in the food supply chain.

As secondary exploratory aims, we will: (i) assess quality of life and emotional–affective well-being using validated instruments, in order to identify psychological or social critical issues related to work in the food supply chain; (ii) characterize nutritional status and dietary habits to detect potential deficiencies or excesses; (iii) quantify systemic biomarkers of oxidative stress and circulating serotonin levels; (iv) identify risk classes, i.e., subgroups of workers at potentially higher disease risk due to inadequate dietary patterns and/or exposure to occupational stressors; (v) assess sex-related differences in nutritional status, oxidative stress biomarkers, and psychological outcomes, to inform the potential need for gender-specific preventive or dietary recommendations; and (vi) analyze the standardized phase angle (SPhA) as an integrative marker of cellular health and systemic status, and explore its potential associations with nutritional, biochemical and psychological indicators on an exploratory basis.

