### 3.6. Sample Size and Statistical Analysis

This is an exploratory, two-group study (active workers vs. sedentary workers). We planned a total sample of 40 participants (≈20 per group). A priori calculations were performed with G*Power (v3.1.9.7) to inform feasibility for a two-group multivariate comparison approximating Hotelling’s T^2^ (implemented as a MANOVA with two dependent variables, R/H and Xc/H). Under conventional assumptions (two-sided α = 0.05; target power ≈ 0.80; small-to-moderate multivariate effect), a sample size of 35 is typically adequate; therefore, we set N = 40 to accommodate measurement variability and potential attrition while maintaining balanced groups. Although the sample size calculation is fixed to the primary bioimpedance outcomes, the nutritional, biochemical, and psychological variables will be treated as exploratory secondary outcomes. For these, the study aims to estimate effect sizes and variability and to evaluate feasibility rather than to achieve confirmatory statistical power.

Raw R and Xc will be standardized by height (H) to obtain R/H and Xc/H. For each group, we will compute the mean vector and its 95% confidence ellipse on the RXc plane. The primary comparison between active vs. sedentary workers is the displacement of the mean impedance vector assessed with two-sample Hotelling’s T^2^ (reporting T^2^, *p*-value, Mahalanobis distance, and 95% CI for the mean-vector difference). Visualization will include the RXc-mean graph with group ellipses. Covariate-adjusted MAN(C)OVA models will be used as sensitivity analyses to assess robustness. In addition to age and sex—variables inherently related to BIVA interpretation—analyses will adjust for occupational factors (e.g., type of work tasks, years in role, ergonomic load) and lifestyle habits (e.g., smoking, alcohol consumption, physical activity outside work), which may influence hydration, body composition, metabolic state, or psychological indicators. Contemporary reference/tolerance ellipses for interpretation will follow Campa et al. [52] or the most appropriate sex-/age-specific set for our sample.

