Standardized phase angle (SPhA), adjusted to sex- and age-specific references, will be analyzed as a continuous endpoint. The primary comparison (active vs. sedentary) will use a two-sample t-test. A sensitivity ANCOVA adjusting for BMI (and other prespecified covariates, if applicable) will assess robustness. The proportion of participants with SPhA ≤−1.65 (≈5th percentile) will be compared between groups using χ^2^ or Fisher’s exact test (reporting risk ratio and 95% CI). Secondary exploratory outcomes, deriving from nutritional, biochemical, and psychological domains’ assessment, will be analyzed with χ^2^/Fisher for categorical variables and t-test/Mann–Whitney for continuous variables depending on normality (assessed with Shapiro–Wilk). Effect sizes with 95% confidence intervals will be reported. Age will be included as a continuous covariate in sensitivity MAN(C)OVA and ANCOVA models. Exploratory analyses will also examine age-related associations with bioimpedance, psychological, and biomarker measures.

Exploratory associations among nutritional indicators (SPhA), bioimpedance parameters, oxidative-stress markers, serotonin, and psychological measures will be examined using Pearson or Spearman coefficients as appropriate. No directional hypotheses are pre-specified for these exploratory analyses; findings will be interpreted as hypothesis-generating.

No missing data are expected because all measurements will be collected during supervised in-person sessions. Data completeness will be verified at the time of assessment. If unexpected missingness occurs, analyses will follow a complete-case approach and the extent of missing data will be reported.

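### Derived body masses and water volumes carry no size index and go to an unadjusted two-group test, so these exploratory comparisons mix body size and sex with nutritional status

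*Protocol article*

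**What the plan says.** - **Aim (1.2).** Nutritional status and body composition are to be compared between sedentary and active workers, "as indexed by bioimpedance-based assessment of body cell mass and hydration".
- **Outputs (3.2.2, within 3.2 Nutritional Status).** The software returns, among others, "total body water, extracellular water, intracellular water, lean mass, fat mass, body cell mass, musculoskeletal mass, appendicular muscle mass". No height or weight index is given for these. The same list also holds items that are not absolute amounts: tissue hydration percentage, nutritional index, phase angle and standardized phase angle (SPhA).
- **Scaling (3.6).** "Raw R and Xc will be standardized by height (H) to obtain R/H and Xc/H". SPhA is referred to sex- and age-specific values. No other bioimpedance output is scaled.
- **Test (3.6).** Secondary outcomes from the nutritional domain are compared by "t-test/Mann–Whitney for continuous variables depending on normality", without covariates.
- **Covariates (3.6).** The sensitivity models name age, sex, occupational and lifestyle factors, and BMI for SPhA. Height is not named.
- **Status (3.6).** Nutritional variables are exploratory. The stated purpose is to estimate effect sizes and variability, and confirmatory power is disclaimed.

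**The concern.** A mass in kilograms or a volume in litres grows with body size. If one group is taller, or has more men, it will show more body cell mass and more water at the same nutritional status. The plan recognises this for R and Xc, which it divides by height, but says nothing for the masses and volumes derived from the same measurement.

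Two things are at stake. An estimated difference in kilograms may be a difference in height or sex mix that is read as better nutrition or hydration. And the spread due to size and sex widens the interval around any real difference. Calling the outcomes exploratory does not remove the first problem, because the effect estimate is itself the intended product. Body cell mass and hydration are also the constructs that the aim names.

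**Working it through.** **The plan's own figures.** The plan gives no power or precision for the derived masses. Its sample-size statement concerns the vector comparison only and is a separate question. The one figure used here is the planned group size of about 20.

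**Assumed inputs (none is in the documents).** Height 1.75 m in men and 1.62 m in women, SD 6.7 cm. Body cell mass 10.8 and 8.8 kg/m². Residual CV of the index 10% (range 8–12%). Mass = index × height². True group difference in the index 9%. Two-sided α 0.05.

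**Step 1: how much of the spread is height, within one sex.** The CV of height² is about 2 × 6.7/175 = 7.7%. The CV of the mass is √(7.7² + 10²) = 12.6%. The share due to height is 7.7²/12.6² ≈ 37%. Over residual CV 12% to 8% it is roughly 30% to 50%.

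**Step 2: how much is sex.** Mean body cell mass is 10.8 × 1.75² = 33.1 kg in men and 8.8 × 1.62² = 23.1 kg in women, a ratio of 1.43. Height² accounts for (1.75/1.62)² = 1.17 of that ratio. The index accounts for the other 10.8/8.8 = 1.23. Dividing by height² therefore removes only part of the sex gap.

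**Step 3: effect in SD units, one sex.** The SD scales with the mean, so averaged over the two groups it is 1.045 times the reference value. On kg/m², d = 9/(10 × 1.045) = 0.86. On kilograms, d = 9/(12.6 × 1.045) = 0.68.

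**Step 4: simulated power, 20 per group, true 9% difference, CV 10%.**

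| Analysis | Sex random at 50% | One sex |
|---|---|---|
| kg, unadjusted | 22% | 56% |
| kg/m², unadjusted | 46% | 76% |
| kg, sex in model | 53% | – |
| kg/m², sex in model | 73% | – |

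Over CV 8–12% with sex random, power is 21–23% on kilograms, 39–52% on kg/m² and 58–91% on kg/m² with sex. In one sex it is 68–45% on kilograms against 91–59% on kg/m².

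**Step 5: no true difference, but a height gap between groups (one sex, CV 10%).** A 3 cm gap shifts the mass by (1.78/1.75)² − 1 = 3.5%, or 3.5/12.6 ≈ 0.27 SD. A 5 cm gap shifts it by (1.80/1.75)² − 1 = 5.8%, or 0.46 SD. The false-positive rate on kilograms is about 13% and 29%. On kg/m² it stays at 5%. In a mixed sample with sex in the model, kilograms still give about 13% and 28%, so adjusting for sex does not replace scaling for height.

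**Step 6: a second set of assumptions.** Heights 1.76 and 1.63 m, SD 6.5 cm, index CV 8–15%, 0–50% men, male-to-female index ratio 1.0–1.3, true difference 10%. Power is 21–78% on absolute mass, 34–97% on mass/height², and 54–97% on mass/height² with sex. The ordering holds, but the size of the gain depends heavily on the inputs.

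**The case against.** **The comparison is inferred.** No sentence says that body cell mass, lean mass or body water will be tested between groups in kilograms or litres. It follows only from the general rule for nutritional outcomes, and the analysis plan, which is not shown, may fix the form. This stands as a limit. Still, the article does state scaling, tests and covariates for other outputs, and a reader applying it as written would run an unadjusted test on absolute amounts.

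**The main analyses are already scaled.** R/H and Xc/H carry the primary comparison, SPhA is standardized, and the output list includes some relative measures. This stands in full. A reader might infer that the primary result is compromised, but the documents do not support that.

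**These outcomes are declared unpowered.** This weakens a complaint about power alone. Even on a size-adjusted scale, 20 per group has 80% power only for d of about 0.91. It does not answer the confounding of the estimate by size and sex.

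**Sex is as large a driver as height.** This also stands. Sex in the model without any indexing raises power from 22% to 53%, so a remedy limited to indexing would be incomplete.

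**Two stronger readings are tempting.** One is that the tests mainly measure stature. Under the assumed inputs, height explains half or less of the within-sex variance, and in a mixed sample its share overlaps with that of sex. The other is that a real difference can hardly be detected. Power near 10% on kilograms does appear if exactly 10 men and 10 women are forced into each group. But the unadjusted test then has a false-positive rate of about 0.1%, and the protocol plans no such balancing.

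**Conclusion.** The point holds for exploratory outcomes only. As written, the plan would compare derived masses and water volumes without a size index, by an unadjusted test, with height in no covariate list. The estimated differences would mix body size and sex with nutritional status and would be less precise than they need to be.

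Under the main assumptions, indexing by height² and adding sex raises power from about 22% to 73% in a mixed sample. Indexing alone raises it from 56% to 76% in a one-sex sample. A height gap of 3 to 5 cm would produce 13% to 29% false positives on kilograms. All these figures rest on assumed heights, CVs and sex mix. What does not depend on them is the direction: absolute amounts carry size and sex into the comparison. The change is worth making, but it does not bear on the validity of the primary comparison.

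**What to change.** In 3.6, add that:

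- body cell mass, lean mass, musculoskeletal mass and appendicular muscle mass are compared between groups as height-squared indices (kg/m²), with sex in the model;
- water compartments are compared in a size-relative form, for example extracellular to total body water;
- absolute kilograms and litres are reported descriptively only.

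Fat mass is in the same list and needs the same decision; a percentage of body weight is one option.

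The cost is wording. Height, weight and sex are needed for the study already. The small downside is that a height-squared index assumes one scaling power. A check model with the absolute mass as outcome and height and sex as covariates would show whether the result depends on it.

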#### 3.2.3. Eating Habits Questionnaire

The participant will also complete a survey on dietary habits, including daily water intake and consumption of other beverages (including alcoholic drinks), adherence to the Mediterranean diet (weekly intake of olive oil, nuts, cereals and whole grains, vegetables, meat, dairy products, processed and industrial foods, chocolate, coffee and tea), as well as the presence of specific dietary regimens and eating habits.

#### 3.2.4. Healthy Eating Education

To promote healthy dietary practices, during the evaluation, we will deliver an informational brochure providing guidance for a healthy lifestyle, based on the principles of the Mediterranean diet and in accordance with the criteria outlined by the National Recommended Energy and Nutrient Intake Levels for the Italian Population [35]. In the brochure, there is a link to the dietary Guidelines from CREA-AN [36]. These guidelines are part of a multifaceted solution to encourage health and prevent diet-related chronic diseases, including cardiovascular disease, type 2 diabetes, some cancers, and obesity. It is a consensus document accepted and endorsed by the scientific community and civil society stakeholders [37].

